### Timeframe

Primary outcomes will be assessed at 6 and 12 months after the completion of an assessment.

Assessment quality will be assessed once the social worker’s assessment has been signed off by the relevant line manager. The relationship between SAAF assessment judgements, overall assessments and CPPs will be undertaken when data are available on all assessments included in the trial, together with analyses of the relationship between the three summary judgements and subsequent maltreatment.

#### Intervening variables

The impact of SAAF on the recurrence of abuse is likely to be mediated by factors that *intervene* between a social worker assessing a family and what happens to that child and family some 6- or 12-months later. Social workers might not feel they have sufficient time to conduct their assessment properly, whether or not they are using SAAF; other professionals may disagree with their assessments, or their assessments may point to interventions that are effective, but unavailable.

We will collect information on a range of potential *intervening variables* as part of our implementation evaluation, and from social workers at the end of each assessment. We will also collect information on the influence that social workers perceive their assessments to have on the decisions of Child Protection Case Conferences (CPCC), including the attention paid to their assessment of risk and the child protection plan/profile of services provided. These data will be sourced from social workers at the end of each assessment, from the SAAF tools (see above), and interviews with child protection chairs and independent reviewing officers.

### Ethical issues

The study was granted ethical approval by the Ethics Committee of the School of Sociology, Social Policy and Social Work, Queens University, on 16 May 2014 (Ref: *EC/167)*.

CSDs are consenting to participate in this study, and have written to the DfE confirming this. CSDs have subsequently confirmed their consent to participate to the principal investigator (PI). All social workers based in the selected teams will be participating as part of their employment. All social workers participating in this study will attend a briefing session with the PI, trial manager, and representatives from DfE and *Child and Family Training*. At this session, the social workers will be given further information about the purpose of the study and their role within it and will be given the chance to ask questions. They will also be provided with a participant information sheet (available from the PI).

On advice from the DfE, consent is not being sought from parents. This is because the focus of the study is the quality of work undertaken by social workers.

### Study timeline

The trial formally commenced on 2 January 2014 (contract agreed). Recruitment by the DfE took place between December 2013 and April 2014.Following a study briefing session, social work teams in each of the participating CSDs will be randomised between May and August 2014. Social workers in the experimental arm in each CSD will receive training in SAAF in groups of 20. Once training is complete in a CSD, all social workers in that CSD will be required to provide information on each of the assessments they complete for a period of 6 months. The flow of work is not always predictable, and this period may be extended in order to obtain the necessary number of cases needed, or foreshortened in the even that this target is reached sooner. Figure 1 provides details of the timeline for each participating CSD.

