### Outcomes

#### Primary outcome

Differences between the two arms in the proportion of cases resulting in maltreatment or recurrence of maltreatment following the completion of an assessment (S17 cases) or initial child protection conference (S47 cases).

*Measures*: using administrative data (CIN data^b^) collected by LA CSDs we will assess the (re)occurrence of maltreatment, as defined by:

 Number of children who become subject to a CPP for a second or subsequent time (or for the first time following a S47 or S17 assessment that did not result in a CPP), as a result of concerns linked to the original assessment; Number of reassessments or re-referrals as a result of concerns linked to the original maltreatment/perceived risk of maltreatment;

At a national level, the CIN data include items such as ‘Initial category of abuse’ and ‘Latest category of abuse’. In order to determine whether or not the trigger incidents are related, that is are indicative of a failed plan or inadequate assessment, data are needed that provide information at a more granular level than that typically collected for the National Statistics Office (the annual CIN return^c,d^). For this purpose we will use the more detailed data gathered by the CSDs (information management) and collect data immediately post-assessment from social workers *via* an electronic questionnaire (the Case Report Form). These data will provide us with information about the concerns of social workers, their confidence in their assessments, their plans and assessments of future risk. They will also ensure that i) we do not miscategorise apparently unconnected events that in fact have a common underlying cause. For example, physical abuse by a parent and sexual abuse by a stranger *may* be unrelated, but they may also be symptoms of a seriously neglectful environment; ii) we can link children who move between one form of assessment or focus to another; for example, S17 to S47, and monitor associated changes in assessment.

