**Table 1 Tab1:** **Scenario planning - power calculations undertaken to inform the sample size**

Scenario	Re-abuse Rate % Control	Re-abuse Rate % SAAF	Unclustered total sample size	Design effect	Clustered total sample size (rounded)
1	50	40	800	1.5	1,200
2a	25	15	510	1.5	770
2b				2.0	1,000
3a	10	5	900	1.5	1,300
3b				2.0	1,800
4a	10	2.5	400	1.5	600
4b				2.0	800
5a	20	10	400	1.5	600
5b				2.0	800

Given the uncertainties in the CIN data, and in the absence of an existing, secure ICC from other studies, we judged that a design effect of 2.0 was most appropriate given the rate of repeat CPPs. This points to the need for an achieved sample size of 1,800 cases, which we estimate will be achieved within a 6-month period following the training of the experimental social workers in each CSD.

The design of the study, including reliance on administrative data, attenuates the need to factor dropout into the calculations.

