### Assignment of interventions

*Sequence generation*: social work teams within participating LAs will be randomly allocated to one of the two study arms. The allocation will be achieved by computer generated random numbers by the Northern Ireland Clinical Trials Unit (NI CTU) using randomly permuted blocks.*Allocation concealment*: the NI CTU will inform the PI and Trial Manager of the allocation of each social work team. The Trial Manager will then Email the designated contact person in each CSD to inform them of their allocation.The Trial Manager will also inform Children and Family Training, who will then liaise directly with the CSD to arrange training for those social workers/teams in the experimental arm.*Implementation*: the allocation to the intervention or control arm will be generated by the NI CTU and conveyed securely to the Trial Manager and PI.*Check on baseline equivalence*: all social workers will complete a baseline questionnaire prior to randomisation, which will provide information on their experience, training to date, expectations of the training, attitudes towards the trial, and so on. This will provide some indication of baseline equivalence between the two arms, as well as informing the interpretation of the study results.*Blinding*: given the nature of the intervention, the data to be collected, and the interface with the Trial Manager (who will be the point of contact for enquiries regarding data collection), it will not be possible to maintain the concealment of allocation, that is social workers will know whether or not they have been trained. Further, the Case Report Form will include questions about the use of the SDM tools (which the control group social workers will not be using) and the assessments that will be quality assessed may include indications that the authors were in receipt of training/used the SAAF SDM tools.

However, we will endeavour to select assessments for audit without divulging the arm from which they were sourced to those conducting the quality assessment. Each CSD will be asked to provide between 25 and 40 assessments, randomly selected by the NI CTU, from participating social workers in each arm, and make these available to the researchers undertaking the quality audit, without divulging which teams the authors belong to.

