### Data management

Case Report Forms will be completed on-line by social workers, using a unique identifier for both the social worker and the family. All data will be stored securely and no identifying details of the family/child will be recorded.

The DfE will flag each child whose assessment is used in the trial to facilitate later follow up, should funding be available. These data will remain anonymised (that is no child’s name would be used).

All data will be monitored using central statistical monitoring for consistency, viability and quality.

Data from the study will only be presented in public once the main results are published in peer reviewed journals according to Consolidated Standards of Reporting Trials (CONSORT) guidelines and disseminated to all the study participants (CSDs) in an accessible format.

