#### Assessing the effectiveness of SAAF

##### Intention-to-treat analyses

The primary outcome analysis will be an intention-to-treat analysis (ITT) such that all cases will be assessed in accordance with the randomisation. Analysis will be conducted both within and across LAs. We will maximise use of administrative data in order to document the extent of differences between the experimental and control groups.

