## Discussion

Staff in children’s social care in England have limited understanding of randomised trials, or experiencing of participating in them. The study was commissioned by the government department responsible for children’s social care; they are keen to adopt robust standards of evidence, but are relatively inexperienced in commissioning randomised trials, one consequence of which is that the timetable set has proved extremely challenging; for example, the need to develop the logic model underpinning the SAAF had not been identified at the commissioning, resulting in subsequent delays to the original timetable. Whilst the source of primary outcome data is administrative, important information is required from the participating social workers, who already feel overstretched. We have sought to minimise all data requests, and briefing sessions are being provided for all teams, to ensure that they understand the purpose of the trial, the implications of randomisation (and why it is important) and what we are asking of them. One of the challenges inherent in this trial is that staff turnover is significant in most CSDs, and many rely on agency staff, but those are the realities of children’s social care at the present time. This is the first study to examine the effectiveness of SAAF. It will add to a currently very limited literature on the contribution that structured decision-making tools can make to improving risk assessment and case planning in child protection and on what is involved in their effective implementation.

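### Cases are identified after randomisation by workers who know their arm, and the ITT case list is tied to no independent source, so arm-dependent filing could go unseen

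*Protocol article*

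**What the plan says.** All references are to the protocol article.

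- **Study timeline.** Teams are randomised after a briefing and the SAAF arm is trained. From then on, "all social workers in that CSD will be required to provide information on each of the assessments they complete" for six months. On the length of the window: "this period may be extended in order to obtain the necessary number of cases needed". It may also be cut short if the target is met early.
- **Primary outcome.** To judge whether a later event is linked to the maltreatment or risk first assessed, the team will use detailed CSD data and will also "collect data immediately post-assessment from social workers" on the Case Report Form.
- **Data management.** "Case Report Forms will be completed on-line by social workers, using a unique identifier for both the social worker and the family". The children flagged for later follow-up are those whose assessments the trial uses.
- **Assignment of interventions (Blinding).** Workers know whether they were trained, and "the Case Report Form will include questions about the use of the SDM tools".
- **Intention-to-treat analyses.** The promise is that "all cases will be assessed in accordance with the randomisation". The list that defines the cases is not named.
- **Sample size, below Table 1.** The design, including its use of administrative data, "attenuates the need to factor dropout into the calculations".
- **Treatment of missing data.** Administrative records are credited with following members of the sample regardless of attrition or compliance.
- **Discussion.** "important information is required from the participating social workers, who already feel overstretched". The same section concedes that turnover is significant in most CSDs.

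**The concern.** In a cluster trial where cases arise after allocation, ITT protects the comparison only if cases are listed in the same way in both arms. Here the reports come from staff who know their arm, after the work that the intervention is meant to change. Reasons for not filing could differ by arm: SAAF is an added task, and the form asks about use of the tools. If unfiled cases also differ in their risk of recurrence, the arms are no longer comparable.

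Two features would hide this. A window governed by a case count lets later reported cases take the place of unreported ones, so a full 1,800 says nothing about completeness. And following outcomes in administrative data cannot restore a case that was never listed. A missing form also removes one of the two sources used to link a later event to the maltreatment or risk first assessed.

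**Working it through.** **1. The plan's own figure.** Scenario 3b of Table 1 (10% v 5%): 900 × design effect 2.0 = 1,800, as stated. The article gives neither alpha nor power. Assuming two-sided 5% and 80% power, the unclustered total is 870 (pooled variance), 864 (unpooled) or 948 (continuity-corrected). The 900 lies between these and has 81.4% power. The point does not depend on this figure; it only gives the effective size used below, 1,800 / 2.0 / 2 = 450 per arm.

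**2. How a case gets onto the list.**
- When: after randomisation and training (Study timeline).
- By whom: the worker, who enters the identifiers (Data management).
- Knowledge of arm: yes (Blinding).
- When collection ends: six months, adjusted to the case count (Study timeline).
- Independent list: none named in the ITT section or elsewhere.

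**3. Is 1,800 likely to be every eligible case?** The six CSDs did 16,395 core assessments in a year, so 16,395 / 2 ≈ 8,200 in six months. Eligible teams handle most complex cases; taking 50–100% gives about 4,100–8,200. Then 1,800 / 8,200 = 22% and 1,800 / 4,100 = 44%. This is rough, because core assessments are only typically the complex ones and the window may close early. It does not show that cases are lost. It shows that the count alone cannot establish completeness.

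**4. Illustrations (every filing and use rate is assumed; true rate 10% in both arms).**

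*(a) Filing depends on SAAF use.* In the SAAF arm 70% of cases use SAAF (rate 8%) and 30% do not (rate 14.67%): 0.7 × 8 + 0.3 × 14.67 = 10.0%. Users file 90%, so 0.7 × 0.9 = 0.63 of all cases are filed user cases. Control filing is 90% and unrelated to outcome.
- Non-users file 60% (0.3 × 0.6 = 0.18): (0.63 × 8 + 0.18 × 14.67) / 0.81 = 9.5%.
- Non-users file 40% (0.3 × 0.4 = 0.12): (0.63 × 8 + 0.12 × 14.67) / 0.75 = 9.1%.

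The spurious benefit is 0.5–0.9 points. The standard error of the difference is √(2 × 0.1 × 0.9 / 450) = 2.0 points.

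*(b) Filing depends on later recurrence, SAAF arm only.* Observed rate = 0.1·f₁ / (0.1·f₁ + 0.9·f₀), with f₁ the filing rate for cases that later recur and f₀ = 0.9 for the rest.
- f₁ = 0.7: 0.07 / (0.07 + 0.81) = 8.0%.
- f₁ = 0.5: 0.05 / (0.05 + 0.81) = 5.8%.
- f₁ = 0.9: 0.09 / (0.09 + 0.81) = 10%, no bias.

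The chance of a false finding for SAAF is Φ[(d − 1.96·SE₀) / SE₁], where d is the spurious difference, SE₀ the pooled and SE₁ the unpooled standard error at 450 per arm. It is 19% for f₁ = 0.7 and 64% for f₁ = 0.5, against 2.5% with equal filing.

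**5. Same selection in both arms.** If control workers also file 70% and 90%, both arms read 8.0% and the difference is zero. If only the control arm is selective, the bias runs against SAAF.

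**The case against.** Much of the opposing case stands.

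- No section makes the Case Report Form the entry rule. Study timeline states a reporting duty, and it explains the flexible window by uneven workload, not by missing forms. The quality audit is triggered by 1,800 completed assessments, not by forms. The case-flow figure is not available here.
- Reporting is required in both arms, and CSDs had to agree to enforce it in order to take part. This lowers the risk but does not measure completeness.
- A reader might infer that cases of workers who do not use SAAF leave the ITT set. The article does not support that. The form's questions on tool use presuppose that non-users file, fidelity is to be described, contamination is an ancillary analysis, and per protocol is only a sensitivity analysis.
- A reader might also infer that a leaver's case is lost. All workers in eligible teams are covered, agency staff included, so whoever completes the assessment must report it. It is lost only if nobody does.
- Linkage does not rest on the form alone, since detailed CSD data are also used. Nor are administrative data incapable of repairing the gap: a CSD listing is exactly what would do so.
- The plan will examine missing cases as well as items, and balance in case types. That helps, but a missing case can be counted only against a list that includes it.
- Analysis-set definitions are often left to the full protocol or SAP. That would answer a complaint about absent detail alone. Here, however, the article itself fixes worker reporting and a count-driven window, and draws a conclusion about dropout that covers only children already in the sample.

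**Conclusion.** The concern holds in a limited form. Cases are identified after randomisation by unblinded workers, collection is steered by a count, and no independent list stands behind the ITT set. Arm-dependent filing related to outcome could therefore make the comparison selectively incomplete without showing in the total, and the statements about administrative data do not cover that loss.

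The size cannot be derived from the documents. The illustrations run from 0.5–0.9 points (under half a standard error) to 2.0–4.2 points, set against a planned difference of 5 points. They rest wholly on assumed filing rates and on control filing being unrelated to outcome; similar selection in both arms would shrink or remove the bias. The stronger reading, that the ITT set is in effect a per-protocol set in the SAAF arm, is not supported. This is a cheap improvement to the design, not a demonstrated bias.

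**What to change.** 1. In Intention-to-treat analyses, define the set as every S47 or complex S17 assessment completed by a randomised team within that CSD's window. List it from CSD records with the same type and duration coding in both arms, whether or not a Case Report Form was filed.
2. Count the 1,800 on that list, and use the list to decide when a window closes.
3. Report form return by arm.
4. Add a sensitivity analysis of any subsequent Child Protection Plan, which needs no form.
5. Limit the dropout sentence under Table 1 to outcome follow-up of cases already in the sample.

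The cost is wording plus a list extract from each CSD, which already supplies detailed data for the primary outcome. The list should be in place during accrual, because it governs the count and collection has begun in one CSD (Trial status at publication). There are two downsides: some listed assessments may not be clearly complex, and linkage for cases without a form rests on CSD data alone.

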**Figure 1 Fig1:**
[figure not shown]
**Flow of cases/Safeguarding Children Assessment and Analysis Framework** (**SAAF) trained social workers within each Children’s Services Department (CSD).**

### Sample size

The sample size was calculated using one of the two measures of the primary outcome - maltreatment, repeat CPPs. Of the two measures (the other being re-referral), this was judged to be the most valid measure of re-abuse within the Children in Need (CIN) Database, the source specified by the funder, the DfE. Re-referrals include large percentages of children in need, but not in need of protection; for example, day care, play groups, family support. Data on these indicators can be found in SFR45-2013^b^.

Children who are deemed in need of protection (that is, are assessed as at risk for significant harm) are subject to a CPP. This sets out what is needed to protect the child and to address the causes of significant harm or risk of significant harm. A successful CPP should remove the threat of significant harm, or reduce it to a threshold that professionals believe can be managed without a CPP. Children who are subject to a second CPP are likely to have been subject to repeat maltreatment, or to be children for whom concerns have increased following the first CPP. The need for a second CPP (or a CPP following an assessment that has judged a child not to require one in the first instance) may indicate a poor quality assessment.

A number of factors make it difficult to arrive at precise power calculations, namely:

 the lack of an available inter-cluster correlation (ICC) for this purpose; variation in size of clusters (range 6 to 12); different rates of CPPs amongst participating CSDs (range 13.2% to 17.5%); inability to estimate re-referrals and repeat CPPs within the time frame of the study; for example, amongst repeat CPCCs, there are no data on time to repeat CPCC, and most CSDs indicated that this would be rare ‘within the year’^e^, and the complexity of the relationship between S17 and S47 assessments, given that one case may have recorded 2 separate assessments.

Together, in the year ending 31 March 2013, the 6 participating CSDs undertook: 8,524 S47 enquiries; 16,395 core assessments^a^ and 5,394 CPCCs.

Table 1 documents a range of scenarios reflecting various postulated rates of re-abuse in the control group, and varying the design effect (variance inflation factor) from 1.5 (based on an estimated ICC of 0.1 and a cluster size of 6 social workers *per* team) to 2 (which allows, with the same ICC, roughly for an increase in cluster size to 10 to 12 social workers *per* team).

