##### Multilevel models

If appropriate, we will also employ nested modelling techniques for random effects models (such as ML-win), as well as comparing the results with a fixed-effect model. Multilevel logistic regression models will be used to assess between group differences (experimental and control) in relation to the probability of abuse recurrence for cases, accounting for the fact that cases are clustered within social work teams.

Ancillary analyses will assess the extent to which:

 rates of abuse recurrence vary according to: rates of staff turnover, severity of initial maltreatment, and the presence of SAAF trained social workers in the control arm affects rates of recurrence (with similar analyses conducted on the effect of untrained workers on experimental group).

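### The design effect uses social workers per team as the cluster size although cases are counted and analysed, so the stated basis for 1,800 cases fails unless workers average about one case each

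*Protocol article*

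**What the plan says.** All references are to the protocol article.

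- **Unit randomised** (Assignment of interventions): "social work teams within participating LAs will be randomly allocated to one of the two study arms".
- **Design effect** (Sample size): it runs "from 1.5 (based on an estimated ICC of 0.1 and a cluster size of 6 social workers" per team, up to 2, which allows "roughly for an increase in cluster size to 10 to 12 social workers" per team at the same ICC. The same section lists "variation in size of clusters (range 6 to 12") among the difficulties, which matches these worker counts.
- **Choice made** (text below Table 1): "we judged that a design effect of 2.0 was most appropriate given the rate of repeat CPPs". Then: "This points to the need for an achieved sample size of 1,800 cases". This is scenario 3b: 10% v 5%, 900 unclustered, 1,800 clustered.
- **Unit analysed** (Multilevel models): the logistic models give the probability of recurrence for cases, "accounting for the fact that cases are clustered within social work teams".
- **Data collection** (Study timeline): each worker reports every assessment completed over 6 months. The period may be lengthened, or cut short once the target is met.

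The article gives neither the number of teams nor the expected cases per team, and it nowhere converts workers to cases.

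**The concern.** A design effect inflates a count of analysed units for the correlation between units in the same randomised cluster. Here the analysed unit is the case and the cluster is the team, so the cluster size has to be cases per team. The plan enters workers per team and then applies the result to a count of cases.

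If workers contribute several cases each, the true design effect at the stated ICC exceeds 2.0, and the 1,800 cases carry less information than the 900 independent cases they are meant to represent. A non-significant result might then reflect too few teams rather than a lack of effect. Because the information is limited by the number of teams, lengthening data collection might not repair it.

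**Working it through.** **Inputs from the article.** ICC 0.1; 6 and 10 to 12 workers per team; 10% v 5%; 900 unclustered; design effect 2.0; 1,800 cases.

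**Assumptions.** Two-sided 5% test, equal arms, equal team sizes. The article states neither the significance level nor the power behind Table 1. The number of teams K is unknown and is shown as a range.

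**Step 1: reproduce the plan's figures.** DE = 1 + (m − 1) × ICC.
- m = 6: 1 + 5 × 0.1 = 1.5.
- m = 10, 11, 12: 1.9, 2.0, 2.1.
- 900 × 2.0 = 1,800.

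The plan's design effects appear when m is the number of workers. The usual pooled two-proportion formula at 80% power gives 870 in total for 10% v 5%, which the plan's 900 slightly exceeds. Power at 900 is 81%.

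**Step 2: number of teams at which the plan's figure holds.** DE = 2.0 at ICC 0.1 needs m = 1 + 1.0/0.1 = 11 cases per team, so K = 1,800/11 ≈ 164 teams, or about 27 per department. With 6 to 12 workers each, that is about 980 to 1,970 workers (164 × 6 = 984; 164 × 12 = 1,968) supplying about 1.8 to 0.9 cases each.

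**Step 3: recompute with cases per team.** m = 1,800/K; effective N = 1,800/DE; ICC 0.1; power for 10% v 5%.

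| Teams K | Cases per team m | DE | Effective N | Power |
|---|---|---|---|---|
| 30 | 60 | 6.9 | 261 | 33% |
| 50 | 36 | 4.5 | 400 | 48% |
| 100 | 18 | 2.7 | 667 | 69% |
| 150 | 12 | 2.1 | 857 | 79% |
| 164 | 11 | 2.0 | 901 | 81% |

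Unequal cases per team would raise DE further.

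**Step 4: ceiling on information.** As cases per team grow, effective N approaches K/ICC but does not exceed it. At ICC 0.1, an effective 900 needs more than 900 × 0.1 = 90 teams. Below 90, no number of cases reaches it.

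**Step 5: sensitivity to the ICC.** Power for 10% v 5% at 1,800 cases:

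| ICC | 30 teams | 50 teams | 100 teams |
|---|---|---|---|
| 0.01 | 89% | 93% | 96% |
| 0.02 | 78% | 87% | 94% |
| 0.03 | 68% | 80% | 91% |
| 0.05 | 53% | 68% | 84% |
| 0.10 | 33% | 48% | 69% |

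The ICC at which DE is exactly 2.0 is 1/(m − 1): 1/59 = 0.017 with 30 teams, 1/35 = 0.029 with 50, and 1/17 = 0.059 with 100.

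**Step 6: detectable difference, one example.** With 50 teams and ICC 0.1 (effective N 400), 80% power corresponds to about 10% v 3.1%.

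**The case against.** The strongest reply is that the ICC of 0.1 is only a placeholder. The Sample size section says that no ICC was available, and the text below Table 1 presents 2.0 as a judgement. Randomisation is stratified by site and site differences are to be modelled, which may lower the ICC that matters. With a smaller ICC, 1,800 cases may be enough. This stands as an argument about the value of 2.0. It does not rescue the derivation, because the article ties both design effects to the same ICC and to workers per team.

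A reader might infer that 1,800 cases certainly fail to deliver the comparison, or that the trial could not detect a halving of re-abuse. The documents support neither. The number of teams is not given, and at about 150 to 164 teams power is 79% to 81% even at ICC 0.1. With fewer teams the result is reduced power, not inability.

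A reader might also take the 16,395 core assessments a year as proof of many cases per team. That does not follow, because collection may stop once the target is reached. Mean cases per team are then about 1,800 divided by the number of teams, whatever the departments' workload.

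Finally, the section on assessing trial validity already plans a check of achieved power, and the multilevel model addresses clustering in the analysis. Both lessen the risk that a null result is misread. Neither restores power or corrects the planning figure.

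**Conclusion.** The unit error is explicit in the text and needs no outside assumption: workers per team were entered where cases per team belong. The stated justification for 1,800 cases is therefore invalid unless workers average about one case each.

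The size of the consequence is conditional. At the plan's own ICC, the 10% v 5% comparison keeps roughly its intended power only with about 150 to 164 teams or more, and falls to about a third with 30. At ICCs of about 0.03 or less with 50 teams, 1,800 cases are adequate. These figures rest on the assumed two-sided 5% level, equal arms and equal team sizes. The sample size itself may prove sufficient; what is wrong as written is its basis.

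**What to change.** Recompute the design effect as 1 + (mean cases per team − 1) × ICC. Use the actual number of teams, which is known because the trial status section says that all have been randomised. Add an allowance for unequal team sizes, and show the result over a range of ICCs, for example 0.01 to 0.10.

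Then replace the present justification with two statements: the power or detectable difference that 1,800 cases deliver across that range, and the ICC at or below which 1,800 cases suffice for 10% v 5%.

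The cost is one recalculation and a revised paragraph. At the higher ICCs the stated detectable difference may become less favourable. No extra cases or teams are required.
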